**Figure 1 fig1:**
[figure not shown]
Flowchart of participants through the IcPAB program.

**Figure 2 fig2:**
[figure not shown]
Intervention schedule for enrolment and assessments (SPIRIT Figure).

### Intervention

2.2

#### Development of the intervention

2.2.1

Development of the intervention is facilitated through six steps. The conceptual design of mapping COM-B onto the suggested research work and the specification of each target behavior in developing and implementing the intervention is provided in Supplementary material S3.

Step 1: Systematically reviewed RCT-based IcPAB interventions for primary school students to identify the current practices at the global level. The review findings have been published elsewhere (37) by recommending the use of COM-B model as the theoretical basis for designing IcPAB interventions.

Step 2: Conducted semi-structured interviews with 21 primary school government teachers in Sri Lanka to analyse their perceptions on implementing IcPAB among Grade five students. The interview findings, which was thematically analyzed based on the COM-B model have been published elsewhere (20).

Based on the review (37) and the interview findings (20), the intervention was developed by embedding the Capability, Opportunity, Motivation-behavior (COM-B) model (20, 42, 48–50). The underlying theory of the COM-B model mentions that outcome behaviors must be understood in their context with consideration given to the individuals’ existing capability, opportunity and motivation to achieve these target behaviors (38, 42, 48, 51, 52). For example, it should be mentioned that the COM-B factors have been considered in IcPAB intervention and how they are addressed through the behavior change techniques (BCTs) (38, 53–55), which are defined as the active, observable, replicable, and irreducible components (42, 54) of the COM-B model.

Step 3: Identify the related COM-B that must be addressed to develop and implement the IcPAB. For example, as explicated in Table 1, it was identified that the class teachers’ dress code as a physical capability-related factor that should be concerned of when designing the IcPAB activities. Because teachers highlighted that they would have physiological limitations to demonstrate IcPAB as they are not wearing sports friendly wear at the classroom.

**Table 1 tab1:** Utilizing COM-B and BCTV1 taxonomy to develop and implement the intervention based on interview findings.

Based on interview findings: What encourages seated learning OR hinders implementing physically active teaching inside the classroom?	Which model of behavior sources (COM-B) is related to the interview finding?	What should be done to introduce IcPAB intervention by improving the identified behavior source model?	What behavior change techniques from BCTTv1 should be applied to activate the intervention functions and policy categories?
Physiological limits due to the age and dress code	Physical Capabilities	Provide examples from the field of education of how IcPAB can be used regardless of the physiological barriers.	4.2 Information about antecedents 5.3. Information about social and environmental consequences 9.1 Credible source 15.1 Verbal persuasion about capability, i.e., *Provide credible written materials and videos of how previous IcPAB practices are conducted despite teacher age and dress; tell teachers individually that they can successfully conduct IcPAB frequently*
		Convince the teachers that the IcPAB can be implemented without changing into a sporty dress.	6.1 Demonstration of the behavior 15.1 Verbal persuasion about capability, i.e., *Show the teachers in a real class situation how IcPAB can be done with the dress code for lady teachers (Saree); tell teachers individually that they can successfully conduct IcPAB frequently.*
Lack of psychological confidence to implement physical activities other than the specified activities in the teachers’ guide.	Psychological Capabilities	Provide easy-to-understand written and visual manuals on conducting IcPAB.	4.2 Information about antecedents 9.1 Credible source, i.e., *Provide a manual specifically designed for Sri Lankan teachers with pictures and videos.*
		Provision of regular training and feedback on IcPAB implementation.	4.1 Shaping knowledge 6.1 Demonstration of the behavior 15.1 Verbal persuasion about capability, i.e., *Hold special training sessions for teachers, advise and agree on how to perform IcPAB; Implement IcPAB with teachers/ provide assisted delivery; provide weekly feedback to the teacher and tell them they can successfully conduct IcPAB frequently.*
Not receiving external enablement to conduct classroom-based physical activities.	Social Opportunities	Request school-level policy decisions to implement IcPAB.	1.2 Problem-solving, i.e., *Hold meetings and request permission from section heads to implement IcPAB as a novel teaching strategy and to test its effectiveness on academic achievement.*
		Set goals to achieve a minimum number of IcPAB daily.	1.1 Goal setting (behavior) i.e.*, Set a goal to implement 5-min IcPAB at least thrice daily.*
		Regular follow-up and monitoring of the fidelity.	7.1. Prompts/ cues 2.2 Feedback on behavior, i.e., *Send daily WhatsApp messages to teachers to implement IcPAB at least three times; monitor the way the teachers conduct IcPAB and provide informative, evaluative feedback.*
Most classrooms are crowded and need more space to conduct physical activities.	Physical Opportunities	Convince the teachers that the IcPAB can be implemented in a small space just by standing in front of the desk.	6.1 Demonstration of the behavior 15.1 Verbal persuasion about capability, i.e.*, Show the teachers in a real class situation how IcPAB can be done just by standing behind the desk; tell teachers individually that they can successfully conduct IcPAB frequently.*
Not receiving updated information on the risks of prolonged sitting	Automatic Motivation	Provide examples of the risks of prolonged sitting and the benefits of doing IcPAB.	5.1 Information about health consequences 5.3. Information about social and environmental consequences 9.1 Credible source, i.e., *Provide credible written materials and videos on the risks of prolonged seating and how such risks can be minimized.*
Lack of strong will to break sitting time and belief in the benefits of engaging in PA inside a classroom	Reflective Motivation	Convince the teachers with evidence that the IcPAB are integrated into the curriculum and that the activities help enhance academic performance.	4.2 Information about antecedents 5.3. Information about social and environmental consequences 9.1 Credible source, i.e., *Provide credible evidence from previous research findings on how IcPAB helped enhance student performance in various subjects.*

Step 4: Applied the BCTs from the BCTv1 taxonomy to mitigate the identified behavioral issue (Table 1) to enhance academic achievement, movement behaviors and the health outcomes of the target group. For example, it was identified that the teachers’ doubts on physical capability factors such as dress code-related physiological limits can be mitigated by providing credible written materials and videos of how previous IcPAB practices are conducted despite teacher age and dress (BCT 9.1) and telling teachers individually that they can successfully conduct IcPAB frequently (BCT 15.1). Further details are provided in 2.2.2 below.

Step 5: Designed IcPAB activities and facilitator packs with local educators based on the evidence collected from the review and the interviews. For example, a manual, logbooks, timers, WhatsApp messaging group and 20 IcPAB cards were prepared as intervention materials. The details of IcPAB cards will be illustrated in 2.2.2 below.

Step 6: Tested the IcPAB cards in a pilot test with two teachers from two classes in one school. This school will not be involved in the main intervention. The aim of this pilot is to test the ability of the teachers to follow the instructions provided on IcPAB cards and to observe the students’ reaction toward the activity breaks.

Step 7: As elaborated in 2.2.2, conduct a training for the intervention class teachers to be familiar with the IcPAB program.

The first six steps were completed, and the Step 7 will be facilitated in future.

#### Delivery of the IcPAB in the intervention group

2.2.2

The IcPAB program will introduce 20 cards among all intervention classes. The interviews (20) conducted during the intervention development stage (Step 2 in section 2.2.1) explored that activities which take around 5 minutes would be feasible to implement in class due to high density of teaching content in each regular class. Also, the previous evidence assured IcPAB, which requires less than 5 min to provide positive intervention effects (12, 56). Therefore, the teachers will be requested to implement at least five-minute PA breaks three times daily. Each activity should be implemented for at least 5 minutes.

The IcPAB cards can be incorporated into the mathematics and language reading lessons. All the cards are designed for teachers to teach mathematics and language lessons using physically active teaching methods while reducing the fifth graders’ school day seated learning time without interrupting academic teaching time. The nature of the activities will also assist students to improve their aerobic fitness and enjoy learning by forgetting any stressors. Each card has a picture resembling a particular IcPAB. The back of the card has written instructions on performing the activities in addition to the instructions provided in the IcPAB manual. The manual was designed for Sri Lankan teachers with pictures by merging the activities with the fifth-grade curriculum with PA.

The first card is designed to implement a breathing exercise as students require stress relief. Hence, the teachers can choose either the first IcPAB card with another card as the first activity of each day or another activity card. Even if the teachers decide not to use the IcPAB card one, they are given instructions on each card to do a little breathing before starting any activity if deemed necessary. Teachers are reminded on each card to use encouraging words (such as very good) to finish the activity and refer to the lesson.

For example, as provided in Supplementary material S4, the first card (IcPAB card ID: IcPAB 3) is designed to help the students with arithmetic skills. If a teacher wants the students to relax by doing a breathing exercise, the students will be instructed to stand comfortably and inhale- exhale three times by raising up and down on the toes while moving the hands up and down in the same rhythm. Then, the students will solve a multiplication problem given by the teacher (if the problem is more complicated, ask students to use a piece of paper while standing) and jump on the spot equal to the obtained answer. Next, the teacher will repeatedly solve the question with the students and jump on the place. The students will be given a verbal appreciation with or without a clap.

The teacher training (BCT 6.1) will be the primary enablement of the teachers to engage in the intervention. Teachers involved in the intervention will receive one-hour training 1 week before the commencement of the IcPAB intervention. The principal investigator will conduct the training session in a classroom after the regular school time upon the teachers’ availability. Teachers will receive intervention materials such as the IcPAB manual, IcPAB cards, timers, and the logbook. Intervention materials are written in the local language (Sinhala). However, English terms are used in the materials when deemed necessary.

By addressing the findings from the interviews (20), the training session with the application of the BCT taxonomy (i.e., BCT 4.1; 4.2; 5.1; 5.3; 9.1) will cover (1) the importance and benefits of IcPAB by referring to previous research findings, (2) rationale of introducing the current IcPAB activities, (3) recording of the logbooks (4) demonstration of IcPAB and (5) questions and answer round. i.e., at training, teachers will be given credible written materials and videos of how previous IcPAB practices are conducted despite teachers’ age and dress (BCT 4.2; BCT 5.3 and BCT 9.1). The teachers will be convinced that the IcPAB can be implemented without changing into a sporty dress by demonstrating some activities during training in addition to the assisted delivery in the classroom (BCT 6.1). Also, teachers will be convinced about the risks of prolonged seating and how such risks can be minimized through IcPAB can be used (BCT 5.1; BCT 5.3 with research evidence (BCT 9.1) in addition to how IcPAB helped enhance student performance in various subjects (BCT 4.2 and 5.3) in other countries.

The principal investigator will deliver and observe the IcPAB program during the first two weeks of intervention to ensure adherence to the intervention protocol by following a previous practice (12). Therefore, extensive demonstrations of the active break activities will not be provided during the training. i.e., Following a previous intervention practice called assisted delivery (12), the principal investigator will deliver the intervention activities together with classroom teachers during the first week of the intervention. During the second week, the principal investigator will observe teachers doing the activities and provide support if needed. This assisted delivery method (BCT 6.1, BCT 4.1) during the first week of the intervention and the IcPAB manual (BCT 9.1) will enable the teacher to engage in the intervention activities continuously. Teachers are given the opportunity to replicate/ modify the PA breaks. If this is done, the teachers will record their actions in the logbook while noting the detailed information on the last pages of the IcPAB manual. Replicated/ modified activities will be given feedback by the principal investigator.

Additionally, prompts (BCT 7.1) such as WhatsApp messages and interactive discussions (BCT 15.1) with the teachers will be used as techniques to implement the intervention to remind and persuade them to carry out the IcPAB each week at least to meet the minimum required dose (BCT 1.1). Furthermore, should the teachers face any difficulty, they will be assisted by the principal investigator or the research assistants to manage the issues (BCT 1.1) while providing informative, evaluative feedback (BCT 2.2) about their progress with the intervention activities. The feedback will also include the satisfaction of students.

However, should the children or the classroom teachers not want to implement intervention activities, they can do so without any reason. No participants will be advantaged or disadvantaged in any way by doing so. Parents, children, and teachers will be reassured that they can withdraw their permission anytime during this project without penalty. No foreseeable added risk was identified above the risks of everyday life. In addition, implementing IcPAB would not harm the students’ physical and emotional health or the pure educational time as the teachers will be given complete autonomy to choose the most appropriate time to carry on IcPAB.

#### Control group

2.2.3

The classes that will be randomized in relation to the control group will not receive the IcPAB within 12 weeks of the intervention. However, those schools will be given all the resources to implement IcPAB activities once the post-test data collection is fulfilled. During the intervention period, the control group’s teachers will be contacted once weekly through WhatsApp phone calls by the principal investigator and twice a week physically by the principal investigator/ research assistants. Correspondence will be maintained to obtain information about their lesson delivery patterns to ensure that the control group did not receive interventions to change their normal study modes.

### Measurements

2.3

Synthesis of primary (academic achievement) and secondary outcomes (movement behaviors and health outcomes) measurements in this study are shown in Supplementary material S5. All measurement outcomes will be compared among the control group. Data collection for measuring outcomes will be conducted by adhering to the Helsinki Declaration, national and school-level safety protocols and COVID-19 prevention guidelines.

#### Primary outcomes

2.3.1

Based on the interviews conducted with 21 teachers from the nine provinces of Sri Lanka (interview findings were published elsewhere; (20)), mathematics and reading performance were identified as the most important subjects for the students to perform well at the Grade Five national level scholarship examination. In the Sri Lankan and international contexts, it is evident that mathematics and reading performance are the key pillars of elementary education’s academic achievement (10, 12, 32, 33, 57).

##### Mathematics achievement

2.3.1.1

Mathematics achievement will be evaluated through a curriculum-based standardized test designed by the teaching officers experienced in Grade five mathematics performance-related evaluation. This test will consist of 60 questions to assess the expected performance of a given term. Students will complete the test within 45 min. The principal investigator and the classroom teacher will collaboratively administer the test.

##### Reading achievement

2.3.1.2

Reading achievement will be evaluated through a standardized reading test specific to the Sri Lankan Grade Five curriculum. Three grade five teachers have chosen two paragraphs to be used at the baseline and at the end of the intervention to evaluate the students’ reading achievement. The paragraphs include around 200 to 250 words; each student will read the sections for 2 minutes. Reading performance will be evaluated by a teacher who is not the student’s classroom teacher (yet a classroom teacher of the same school’s parallel grade) under the principal investigator’s distant observation.

#### Secondary outcomes

2.3.2

Movement behaviors such as PA levels, steps count, and sedentary behavior within regular school hours will be evaluated. Health outcomes such as BMI, aerobic fitness, and perceived stress will be assessed as other secondary outcomes.

##### Movement behaviors

2.3.2.1

Objective data for the light physical activity (LPA), moderate physical activity (MPA), vigorous physical activity (VPA), MVPA, steps count, and sedentary behavior will be measured during regular school hours using waist-worn accelerometers (GT3-X triaxial model, ActiGraph LLC, Pensacola, Fla., USA). Accelerometer data will be collected for a week at baseline and the post-test (week 13).

The accelerometers will be distributed by the teachers to the students randomly on the first school day and collected back on the fifth school day of the week. The research team will demonstrate to the teachers and the students how the accelerometers should be worn on the first day. However, due to the limited number of accelerometers, this study will use a randomly selected subsample (n = 47) to collect data to measure all the movement behaviors following previous research practice (12, 34, 58, 59). After accelerometers are randomly distributed to the students on the first day, the teachers will prepare a list assigning each student to a specific numbered accelerometer to ensure that the same child wears the same device every day during all the data collection stages. Then, the research team will receive another version of the same list where the students’ anonymous identification number is related to the accelerometer. The classroom teacher will also record absent students assigned with an accelerometer, and a researcher assistant will verify the data during the school visits.

Based on previous research practices (12, 60), only the accelerometer data, which will be identified for wearing more than five school hours on at least one school day, will be included in the analysis for intervention effects (12, 60). Following the standard practices in the studies involving children, non-wear time will be defined as 20 min of consecutive zeros (12, 31, 61). Freedson cut points will be used to classify movement behavior intensities based on the data collected in 15-s epochs (12, 62). Due to the focus on in-school PA, a longer wear time is not deemed necessary for the current study, as recommended by recent scholars (63). To confirm in-school wear-time for valid days, a further visual check of each accelerometer profile will be undertaken (63). Therefore, research assistants will randomly visit the schools during the data collection week to ensure that the students wear the same device accurately during school hours.

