Therefore, there is a need for more IcPAB initiatives integrated into the curriculum across different geographic locations/ cultures (37) that require shorter bouts of time [i.e., around 5 minutes (12, 43)] with strong methodological quality (39, 44), outcome and process evaluation procedures and theoretical underpinnings (37, 39, 44). Also, the moderating effects of gender on the intervention should be further examined. Thus, by addressing the research limitations, this study aims to develop, implement, and evaluate a 12-week IcPAB program among grade five primary school children in Sri Lanka.

Depending on the aforementioned rationale, the specific research questions of this study include: (1) What is the impact of the IcPAB intervention on the primary outcome, academic achievement (mathematics and reading achievement) during the school day? (2) What is the impact of the IcPAB intervention on the secondary outcomes, movement behaviors (PA levels, steps count and sedentary behavior) and health outcomes (BMI, aerobic fitness, and perceived stress) during the school day? It is hypothesized that the IcPAB group will show improvement in all measures compared to the control group.

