### Study design and selection of subjects

2.1

A single-blinded parallel randomized controlled trial (RCT) will evaluate the intervention effects of IcPAB compared to a control group. Target participants will be the fifth graders in government primary schools. Based on the data shared by the Ministry of Health, Sri Lanka, the COVID-19 pandemic severity was slight in the Bandarawela Education Zone (city) in Badulla District. Therefore, the government schools of Bandarawela Education Zone were contacted to initiate the recruitment process in late 2022. The age range of the grade five students is 9 to 10 years old. The targeted population is exposed to 6 hours of regular classroom time (7.30 a.m. to 1.30 p.m.), including a 20-min lunch break according to the government primary school norms in Sri Lanka. Within the government primary school setting, the teacher in charge of a class should teach all subjects in the syllabus for the class, such as mother tongue, mathematics, religion, environment and English. Depending on the interests of the schools, the teachers will conduct additional classes after regular school time to prepare the students for the year-end national scholarship examination. Therefore, the study was designed to be implemented only during the standard classroom time for 12 weeks.

Based on GPower 3.1 software, through *a priori* power analysis, it was estimated to obtain at least 198 participants for both the intervention and control groups to expect an effect size of 0.21 [Cohen’s *f*, converted from *d*, (45, 46)] on academic achievement (mathematics) by providing a power of 0.8 (1-β) with an alpha of 0.05 to test the primary hypotheses of the study with an estimated 10% dropout rate [dropout rates were less than 10% in previous studies (10, 33, 47)] at the post-test/ follow-upstage.

Therefore, it is anticipated to recruit five to six classes (30 to 40 students per class) from two government schools to conduct the study to reach the required minimum sample size. Block randomization technique via MS Excel, will be used to randomize the sample classes by an assessor who is blinded to the intervention content and outcome assessment.

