### Fidelity of the intervention

2.4

The primary source for assessing the fidelity will be the logbooks of the teachers. An example of a log sheet can be found in Supplementary material S6. Teachers will indicate how many IcPAB they implemented daily throughout the intervention period. Teachers will be reminded every day via WhatsApp messages to carry out IcPAB, and a research team member will visit the schools once a week to check if the logbooks are duly filled. The personal visits to the intervention schools will also minimize issues with time management and PA breaks implementation from the teachers’ side. In addition, accelerometer data from the post-test will be compared with the responses obtained through teacher and student interviews at the post-test.

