### Process evaluation

2.5

During the intervention, the principal investigator will receive teacher feedback and give subjective evaluations on how the teachers implement the IcPAB. At the same time, the research team will obtain verbal feedback once a week from the students on IcPAB’s ability to provide fun and engagement using two close-ended questions: (1) Did you enjoy the activities today? (2) Was it easy for you to follow the instructions and do the activities today? This ongoing feedback-receiving process will be used to overcome any identified or foreseen challenges to implement the IcPAB program (31, 43).

In addition, after the 12-week RCT intervention program, a five-point Likert-scale questionnaire will be distributed among the intervention group’s teachers and students to analyse process evaluation outcomes (Supplementary material S7). The teachers’ questionnaire consists of eight items, while the students’ questionnaire consists of nine items. Both the questionnaires were adopted from previous research work (56, 69).

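### The only follow-up accelerometer week is week 13 of a 12-week programme; unless breaks continue in that week, the movement outcomes miss the scheduled break activity

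*Protocol article*

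**What the plan says.** The Introduction gives the aim as to develop, implement and "evaluate a 12-week IcPAB program among grade five primary school children in Sri Lanka". Section 2.1 adds that "the study was designed to be implemented only during the standard classroom time for 12 weeks". The Control group section says that control classes "will not receive the IcPAB within 12 weeks of the intervention", and that materials go to them "once the post-test data collection is fulfilled". The Process evaluation section places its questionnaire at the end: "after the 12-week RCT intervention program, a five-point Likert-scale questionnaire will be distributed".

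On measurement, the Movement behaviors section says: "Accelerometer data will be collected for a week at baseline and the post-test (week 13"). This is the only follow-up recording described. It is confined to regular school hours and to a random subsample of 47 students.

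The second research question in the Introduction reads: "What is the impact of the IcPAB intervention on the secondary outcomes, movement behaviors (PA levels, steps count and sedentary behavior"), together with health outcomes, during the school day. The Fidelity section names teacher logbooks as the primary source, backed by weekly visits, and then adds that "accelerometer data from the post-test will be compared with the responses obtained through teacher and student interviews at the post-test".

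**The concern.** Mathematics, reading, BMI and fitness accumulate over a programme and can sensibly be measured just after it. School-hours activity, steps and sitting differ in kind: they describe what the child does in the hours recorded. The programme acts on them mainly through the breaks, requested at least three times a day for at least five minutes each. The Introduction argues the same way when it cites gains of 18% in steps and 26% in moderate-to-vigorous activity over the school day from activity breaks.

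If the devices are worn only after scheduled delivery, the estimate answers a narrower question than the one posed, namely whether activity stays higher afterwards or whether some teachers carry on unprompted. The protocol neither defines nor controls either. A small or null difference would then say little about whether breaks raise activity while they are being given. The same recording is also used under fidelity. That section needs evidence on delivery, and the Limitations section concedes possible bias because the teachers who deliver the breaks also record them.

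**Working it through.** **Plan's own figure.** The protocol gives no sample size or power for the movement outcomes. Its total of 198 is for mathematics. With f = 0.21, d = 2 × 0.21 = 0.42, and a normal approximation (two-sided 0.05, power 0.80) gives 89 per arm, 178 in total; 178 / 0.90 = 197.8, rounded up to 198. That figure reproduces and does not depend on the accelerometer week.

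**Timeline, side by side.**

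| Item | When, as written | Section |
|---|---|---|
| Delivery of breaks | 12 weeks | Introduction; 2.1 |
| Control classes without breaks | within the 12 weeks | Control group |
| Process questionnaire | after the 12 weeks | Process evaluation |
| Follow-up accelerometry | post-test, week 13 | Movement behaviors |
| Materials to control classes | after post-test data collection | Control group |

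Section 2.2.2 counts the first and second weeks from the start of the intervention. On that numbering delivery fills weeks 1 to 12, and week 13 is the week after.

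**Scheduled contrast between arms.**
- Minimum dose: 3 × 5 = 15 min per day (section 2.2.2).
- School day: 7.30 a.m. to 1.30 p.m. = 360 min, including a 20-minute lunch break, so 340 min without lunch (section 2.1).
- Share: 15 / 360 = 4.2%, or 15 / 340 = 4.4%.
- Recorded dose in a delivery week: 15 min for a student with one valid day (the minimum accepted) up to 5 × 15 = 75 min with five.
- Scheduled dose in week 13, as written: 0 min per day.

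**What dilution could cost (illustration).** Assumptions not in the documents: 47 students split evenly (23.5 per arm), two-sided 0.05, no clustering, a standardised effect d while breaks run, and an effect proportional to the fraction of breaks continuing in week 13, with no other carry-over. The power is that of a two-sample t-test with 45 degrees of freedom and noncentrality fraction × d × √(23.5 / 2). For d = 0.8 and all breaks continuing, the noncentrality is 0.8 × 3.43 = 2.74.

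| Fraction continuing | d = 0.5 | d = 0.8 | d = 1.0 |
|---|---|---|---|
| 100% | 39% | 77% | 92% |
| 75% | 24% | 52% | 71% |
| 50% | 13% | 27% | 39% |
| 25% | 7% | 10% | 13% |
| 0% | 5% | 5% | 5% |

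The last row is the significance level itself. Clustering by class would lower the other rows. The levels depend on the assumed d; the direction does not.

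**The case against.** The strongest reply is that the protocol never says breaks stop after week 12. Week numbering is not defined in the text, and the schedule figure that might settle it is not available here. If the baseline week were counted as week 1, delivery would run over weeks 2 to 13 and week 13 would be the last delivery week. Some of the text also fits continuation. Control classes get materials only after the post-test, intervention teachers are not asked to return theirs, and setting post-test accelerometry against post-test interviews under fidelity makes most sense if breaks are still happening. Activity just after a programme meant to change teachers' behaviour is also a legitimate quantity, if a narrower one.

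Much of this stands, and it makes the point conditional. A reader might infer that breaks have definitely ceased and that the difference between arms in week 13 is zero by construction. The documents do not support that: only the scheduled contrast is zero, and teachers may carry on.

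A reader might also infer that fidelity cannot be verified. That is not supported either. Logbooks are the primary source, they are checked weekly, the principal investigator delivers with teachers in the first week and observes in the second, and the accelerometer comparison is an addition.

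What does not fall away is that the text calls week 13 the post-test of a 12-week programme and schedules no breaks in it. If continuation is intended, it has to be stated.

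**Conclusion.** The point holds in conditional form and should be addressed. On the plain reading, a concurrent behaviour is recorded in a week with no scheduled breaks. Unless breaks continue through that week, the movement outcomes estimate carry-over or unplanned continuation, and the scheduled contrast of at least 15 min per day (4.2% of the full school day, 4.4% without lunch) is not observed. The added accelerometer comparison then cannot corroborate delivery.

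The scope is limited to secondary outcomes in 47 students and one supplementary fidelity element. The primary outcomes and the sample size of 198 are untouched. The conclusion rests on numbering weeks from the start of delivery and on the absence of any statement that breaks run in week 13; a schedule showing otherwise would reduce it to a wording correction.

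**What to change.** Place the follow-up accelerometer week in a delivery week, for example week 12, and leave mathematics, reading, BMI, fitness and stress at week 13. For fidelity, compare the traces with the teacher logbook entries for that same week.

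If week 13 is kept, do one of two things:
- State that breaks continue through the recording.
- Label the movement estimate as post-programme behaviour and remove the accelerometer comparison from the fidelity section.

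In either case, say in the text which week counts as week 1.

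Moving the week uses the same devices and staff and changes no sample size. It gives up the after-programme carry-over measure. One week of recording in 47 students, whichever week is chosen, still cannot verify delivery over all 12 weeks, so logbooks and visits must remain the main fidelity evidence.
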